## Abstract

**Background:**

Achievement of the UNAIDS 90-90-90 targets in Sub-Sahara Africa is challenged by a weak care-cascade with poor linkage to care and retention in care. Community-based HIV testing and counselling (HTC) is widely used in African countries. However, rates of linkage to care and initiation of antiretroviral therapy (ART) in individuals who tested HIV-positive are often very low. A frequently cited reason for non-linkage to care is the time-consuming pre-ART assessment often requiring several clinic visits before ART-initiation.

**Methods:**

This two-armed open-label randomized controlled trial compares in individuals tested HIV-positive during community-based HTC the proposition of same-day community-based ART-initiation to the standard of care pre-ART assessment at the clinic. Home-based HTC campaigns will be conducted in catchment areas of six clinics in rural Lesotho. Households where at least one individual tested HIV positive will be randomized. In the standard of care group individuals receive post-test counselling and referral to the nearest clinic for pre-ART assessment and counselling. Once they have started ART the follow-up schedule foresees monthly clinic visits. Individuals randomized to the intervention group receive on the spot point-of-care pre-ART assessment and adherence counselling with the proposition to start ART that same day. Once they have started ART, follow-up clinic visits will be less frequent. First primary outcome is linkage to care (individual presents at the clinic at least once within 3 months after the HIV test). The second primary outcome is viral suppression 12 months after enrolment in the study. We plan to enrol a minimum of 260 households with 1:1 allocation and parallel assignment into both arms.

**Discussion:**

This trial will show if in individuals tested HIV-positive during community-based HTC campaigns the proposition of same-day ART initiation in the community, combined with less frequent follow-up visits at the clinic could be a pragmatic approach to improve the care cascade in similar settings.

**Trial registration:**

NCT02692027, registered February 21, 2016

## Background

In November 2014 the Joint United Nations Programme on HIV/AIDS (UNAIDS) published the 90-90-90 targets for 2020 [1]. The strategy aims at a massive scale-up in coverage of antiretroviral therapy (ART) among individuals infected with HIV. Based on accumulated evidence that viral suppression through successful ART reduces the risk of transmission [2, 3], it is expected that – if achieved – the 90-90-90 targets would lead to a reduction of the yearly global HIV-incidence from 2 million currently to 500,000 by 2020 [4]. In 2015 two randomized controlled trials showed the benefit of starting ART as early as possible for infected individuals – even if CD4-cell counts were above the threshold of 500 cells/mL [5, 6], leading the World Health Organization (WHO) to recommend that anyone infected with HIV should start ART as soon as possible after diagnosis [7]. A “seek-test-treat” strategy bears, however, unprecedented challenges in settings where HIV is hyperendemic and resources may be limited [8, 9].

The Continuum of Care Cascade (“the cascade”) involves the steps HIV-infected individuals have to take in order to achieve viral suppression. It starts with knowing one’s HIV status, continues with linkage to care after a positive HIV test, initiation of ART, uninterrupted continuation of ART (retention in care and adherence to medication), and ends with sustained viral suppression [10]. Already prior to announcement of the “seek-test-and-treat” approach, weaknesses in the cascade often hampered the effectiveness of HIV programs in resource-rich as well as resource-poor settings [11–13]. In Sub-Saharan Africa the care cascade is still far from the 90-90-90 targets with only 29 % of infected individuals estimated to be on ART and virally suppressed in 2013 [1]. In order to achieve the UNAIDS targets innovative, effective, and practical approaches for improving the care cascade are thus urgently needed [14, 15].

Linkage to care after an initial positive HIV test has been described as the “Achilles’ heel” of the care cascade [16]. Most studies from Sub-Saharan Africa report linkage rates lower than 50 % [17–21]. In a cluster-randomized trial comparing home-based with mobile-clinic HIV testing and counselling (HTC) in Lesotho, only 25 % of newly tested HIV-positive individuals accessed care within 1 month after the test [22].

Several interventions have been shown to improve linkage to care, such as point-of-care CD4 count directly after a positive HIV test [23], immediate start of cotrimoxazole prophylaxis [24], incentives such as food-assistance [25], extended post-test counselling during home-visits, or community-workers accompaniment [26–28]. However, controlled studies testing programmatic intervention packages for improving linkage to care are still largely lacking [29, 30]. Furthermore, it must be noted that interventions, such as patient-accompaniment or food support are resource intensive and may work in small NGO-driven projects, but are not sustainable on a larger scale [31]. In a systematic review addressing barriers for linkage to care, transport cost and distance were the most frequently cited factors for patients not enrolling in care after a positive HIV test [32].

This paper describes the protocol of the CASCADE-trial. This trial tests the effectiveness of same day home-based ART initiation after a positive HIV test in combination with a reduction of the frequency of follow-up visits to the clinic as a pragmatic and programmatically feasible approach to improve linkage to care, retention in care, and viral suppression.

## Methods

### Trial design

The CASCADE-trial is a two-armed open-label randomized controlled trial. Allocation is 1:1 with parallel assignment. The intervention is targeted to individuals who tested HIV-positive during community-based HTC and entails same day community-based ART start combined with less frequent follow-up visits. The intervention arm will be compared to the standard of care in Lesotho (referral to facility for ART initiation followed by monthly follow-up visits). The primary outcomes are linkage to care at 3 months and viral suppression at 12 months after a positive HIV test.

### Recruitment and participants

Participants will be recruited during community-based HTC campaigns in the district of Butha-Buthe, in northern Lesotho. Lesotho has an estimated adult HIV-prevalence of 23.4 %. Among the hyper-endemic countries of southern Africa it has the highest transmission rate and the lowest ART coverage [33]. Butha-Buthe is a rural district with an estimated 110,000 habitants, mostly subsidence farmers or mine workers, or construction or domestic workers in neighboring South Africa. The district has only one small town (Buthe-Buthe, ca. 25,000 habitants), the remaining habitants live in villages scattered over a partly mountainous surface of 1,767 km^2^. According to UNAIDS an estimated 11,000 HIV-infected adult persons lived in the district in 2013 [34].

Home-based HTC campaigns will be conducted for an anticipated period of 3 months beginning at the end of February in the catchment areas of six health care facilities - four nurse-led health centers, one missionary and one public hospital.

For rural areas, villages were randomly selected from a list of eligible villages. A village is eligible if it is clearly confined to the catchment area of one of the six facilities and if it comprises between 40 and 80 households. In Butha-Buthe town urban neighbourhoods were randomly selected.

Three teams consisting of 4 lay counsellors, each supervised by one professional counsellor and a nurse visit all households in selected villages and urban neighbourhoods proposing HTC to all household members. Each house will be visited once during the workweek. During this first visit, lay counsellors enquire about absent household members. If a household member is absent, the household will be visited a second time during a weekend. The HTC-coverage in visited areas will be assessed as part of a nested study (see nested studies below).

If a household member tests HIV positive during the HTC campaign, the study nurse is called to assess whether the individual is eligible for the CASCADE trial. Consenting individuals 18 years or older, living or working in the district of Butha-Buthe, having never been on combination ART and willing to receive follow-up at one of the six study facilities are eligible. Exclusion criteria are: pregnant or breast-feeding, already enrolled in care for another chronic disease, clinical WHO stage 4 or active tuberculosis, or a positive cryptococcal antigen test.

If the sample size will not be reached during the 3 months of home-based HTC campaigns, the recruitment period will be extended and mobile clinics will be set up at urban or rural spots, such as taxi ranks or market places. Procedures for home-based HTC as well as HTC in mobile clinics in Lesotho has been described in detail elsewhere [22].

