### Primary outcomes

The trial has two primary outcomes. The first primary outcome is linkage to care within 3 months after having been tested HIV positive during the HTC-campaign. A patient is considered to have linked to care if he/she attends the clinic at least once within 90 days after enrolment in the trial. The second primary outcome is viral suppression 12 months after enrolment in the trial. Viral suppression is defined as a viral load (VL) <100 copies/mL between 11 and 14 months after diagnosis of HIV-infection.

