### Sample size and randomization

Households will be randomly allocated to a study arm at a ratio of 1:1. A randomization list was generated by an independent statistician with a block size of 4. Sealed and consecutively numbered envelopes containing treatment assignment and study documents are provided to the study nurses. It was not possible for treatment to be blinded.

The sample size for this trial is based on the primary endpoint of linkage to care within 3 months after HIV diagnosis. We expect 3-month linkage to care rates of 40 % in the control and 60 % in the intervention arm. As the trial is randomized at the household level, we require a total of 260 households with at least one HIV-positive participant to detect a 20 % increase in linkage to care assuming a Type I error rate of 5 % and power of 90 %. With an estimated uptake of HTC of 94 %, a prevalence of previously untreated HIV infection during home-based HTC campaigns of 5 %, and a 10 % trial participation refusal rate or choice of alternative health facility, we need to visit 6200 households to achieve the desired sample size of 260 households. In case more than one HIV-positive individual is diagnosed in the household, all individuals meeting eligibility criteria will be included and randomized to the same arm. This will only serve to increase the power of the study.

With the proposed sample size above, we will have sufficient power to test the second primary endpoint of viral suppression at 12 months. As those not linking to care will be considered as failures, we expect viral suppression rates of 25 % in the control arm and 45 % in the intervention arm. With 130 individuals per arm, we will have 93 % power to detect a difference of 20 % in viral suppression rates.

Analysis will be as intention to treat. The study will be analysed using mixed effects logistic regression models in order to account for the clustering of households (if sufficient number of households include more than one HIV-positive individual in the study) and village. If the arms are not found to be balanced on important risk factors for linkage to care and viral suppression, these risk factors will be adjusted for in models. Linkage and viral suppression rates between the control and intervention arm will be presented with odds ratios and 95 % confidence intervals.

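### ART-naive people already in HIV care can be enrolled, and any clinic visit within 90 days scores as linkage, so the first primary outcome could count people who were linked before they entered the trial

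*Protocol article*

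**What the plan says.** Under Recruitment and participants, the counselling teams visit every household in the selected areas, "proposing HTC to all household members". An adult who tests positive, lives or works in the district and consents is then judged against one criterion on HIV history and one on place of follow-up: "having never been on combination ART and willing to receive follow-up at one of the six study facilities are eligible". The only bar that concerns existing care comes at the head of the list of exclusions: "Exclusion criteria are: pregnant or breast-feeding, already enrolled in care for another chronic disease". The remaining items on that list are about severe or concurrent illness, not about being in HIV care.

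Under Primary outcomes, the first primary outcome counts as met by anyone who "attends the clinic at least once within 90 days after enrolment in the trial". It need not be a first visit or a new registration.

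Under Sample size and randomization: "We expect 3-month linkage to care rates of 40 % in the control and 60 % in the intervention arm". The type I error is 5%, the power 90% and the total 260 households, allocated 1:1. Analysis is by intention to treat with mixed effects logistic regression, adjusting for important risk factors for linkage if the arms turn out unbalanced on them.

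**The concern.** The word *another* in the chronic-disease exclusion means other than HIV. The criterion therefore catches a patient attending for a different long-term illness but not one attending the same clinic for HIV before starting ART. No other criterion requires a new diagnosis or asks about current HIV care.

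The rest of the article presumes a person who is not yet linked. The Background frames the problem as what follows an initial positive test and cites a 25% one-month figure in newly tested people. Control and intervention arms describes the control participant's first clinic visit after the test. Primary outcomes and Sample size both date events from the HIV diagnosis. The eligibility rules do not secure that population.

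Two things are at stake. People who would attend whatever their allocation raise the rate in both arms and narrow the difference between them. The control rate, which readers will take as linkage after home-based testing under standard care, would be partly a rate of routine attendance.

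**Working it through.** **Inputs from the article:** linkage 40% (control) v 60% (intervention); type I error 5%; power 90%; 260 households, taken as 130 participants per arm.

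**Assumptions, because the article gives no figure:** a share f of participants is already in HIV care; 90% of these attend within 90 days in either arm; the 40% and 60% apply to everyone else; the test is two-sided.

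**Step 1: reproduce the plan's figure.** With p̄ the mean of the two rates, n per arm = [1.960·√(2p̄(1−p̄)) + 1.282·√(p₁(1−p₁) + p₂(1−p₂))]² / (p₂−p₁)². For 0.40 and 0.60 this gives 129.3, so 130 per arm and 260 in total, as stated. Power at 130 per arm is 90.2%. The sample-size arithmetic is sound.

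**Step 2: mix in people already in care.** The rate in each arm becomes p·(1−f) + 0.9·f, so the difference is 20·(1−f) percentage points. For f = 10%:
- control: 0.40×0.90 + 0.09 = 0.45
- intervention: 0.60×0.90 + 0.09 = 0.63
- difference: 18 points

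**Step 3: power at 130 per arm.** Power = Φ{[(p₂−p₁) − 1.960·√(2p̄(1−p̄)/130)] / √[(p₁(1−p₁) + p₂(1−p₂))/130]}. For f = 10%: (0.18 − 0.1212)/0.0608 = 0.97, and Φ(0.97) ≈ 83%.

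| f (assumed) | Control | Intervention | Difference (points) | Power |
|---|---|---|---|---|
| 0 | 40.0% | 60.0% | 20 | 90.2% |
| 5% | 42.5% | 61.5% | 19 | 87.0% |
| 10% | 45.0% | 63.0% | 18 | 83.3% |
| 20% | 50.0% | 66.0% | 16 | 74.6% |

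The 90% attendance figure matters little. At 100% attendance the powers are 87.0%, 83.5% and 75.2% for f = 5%, 10% and 20%. At f = 2% with 90% attendance, power is 89.0%.

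**Step 4: the other reading of 40% and 60%.** If these are rates for everyone enrolled, with those already in care included, power stays at 90.2% whatever f is. The control rate among people not in care is then (0.40 − 0.9f)/(1−f). At f = 10% this is 0.31/0.90 = 34.4%, or 33.3% if all those already in care attend. The 40% would then overstate linkage after a community test.

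**The case against.** A reader might infer that the outcome does contain already-linked people and that the trial is underpowered. The documents do not support that.

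- **f is unknown and could be zero.** Entry needs a positive test in the campaign, and someone already in HIV care would have to accept retesting. The article refers to another publication for the testing procedures, so how known positives are handled cannot be seen. This stands: the text shows only that such people could be enrolled, and the power table is conditional.
- **The planned rates may already allow for them.** They are given as the expected rates in the two arms, and the household yield is based on previously untreated infection, not on new diagnoses. This stands too. It removes the power loss but not the difficulty in interpreting the control rate.
- **Including them may be deliberate.** The trial targets people who test positive in the community. An ART-naive person in care can still be offered same-day ART and contributes to ART initiation and viral suppression. This is a fair pragmatic argument for those outcomes, but not for linkage, which the person has already achieved.
- **Dilution is towards the null, and adjustment for imbalanced risk factors is planned.** Dilution would not manufacture a positive result. The adjustment helps only if prior care is recorded, and nothing in the article says that it is.

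A reader might also conclude that the main linkage comparison should be restricted to people not in care at baseline. That would take the primary analysis off the stated intention-to-treat population after recruitment has begun, for a limited gain. With 40% v 60% in the reduced sample, power is 88.6% at f = 5% (123.5 per arm, against 87.0% diluted) and 86.9% at f = 10% (117 per arm, against 83.3%). The restriction is better kept as a supporting analysis.

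Condensation in a journal article does not dispose of the point, because both the eligibility rules and the outcome definition are stated outright. The weakness lies in how they fit together.

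**Conclusion.** The concern holds as a gap between eligibility and outcome. As written, an ART-naive person already in HIV care can be enrolled, and a routine visit would score as linkage in either arm. No other part of the article closes this.

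The size is not known. If the planned rates describe people not yet in care, the loss from 90.2% power is about 3 points at f = 5%, 7 at f = 10% and 16 at f = 20%, assuming 90% attendance in both arms. If they already include such people, there is no loss of power, but the control rate is not a rate of linkage after a community test. The stated sample size is not in error, and any dilution would make the trial conservative. The change is worth making because it costs little and settles what the first primary outcome measures.

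**What to change.** 1. For remaining recruitment, add current enrolment in HIV care at any facility to the exclusion criteria.
2. For all participants, including those already randomised, record prior HIV care as a baseline variable: self-report, checked against the six clinics' registers using only entries dated before enrolment. The status then precedes allocation and cannot depend on it.
3. Keep the intention-to-treat comparison of all randomised participants as the primary linkage analysis. Adjust it for prior-care status whether or not the arms look unbalanced.
4. Before outcomes are compared by arm, prespecify a supporting linkage analysis in participants not in HIV care at baseline. Because it is defined by a pre-randomisation characteristic, it remains a randomised comparison. Report the number already in care in each arm, so that readers can see f.

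The cost is one eligibility line, one baseline question, a register check and slightly slower recruitment.

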### Control and intervention arms

The control group follows the standard of care in Lesotho [35, 36] that is similar to most settings in Sub Saharan Africa. During the household visit, individuals found HIV-positive and randomized to the control arm will receive post-test counselling and a referral letter with an appointment at their chosen health facility. On the first visit to the clinic, the participant receives a laboratory assessment (CD4 cell-count, serum creatinine, haemoglobin) and a first adherence counselling session. The participant must then return to the clinic to receive his/her laboratory results and to undergo a second adherence counselling session. Depending on whether the participant is judged as “ready to start ART” by the counsellor at the clinic, he/she may start ART at their second clinic visit or have to attend a third adherence counselling session. Once the participant has started ART, the first and second follow-up visits are scheduled for 14 and 28 days after ART initiation, respectively. Thereafter, follow-up visits are scheduled monthly until 6 months after ART initiation. If the participant is clinically stable, clinical follow-up visits may then be spaced to 3-monthly intervals, but refills of ART must still be collected on a monthly basis.

Participants randomized to the intervention group receive post-test counselling and clinical and laboratory assessment with the possibility of same day ART start combined with a reduced frequency of follow-up visits. Directly after the positive HIV-test result the study nurse assesses the participant clinically and performs point-of-care laboratory testing (serum creatinine (StatSensor Creat®, Nova® Biomedical), haemoglobin (Hemocue®, HB301), and CD4 cell-count (PIMA Alere®)). Thereafter, the participant receives a standardized short adherence counselling. After adherence counselling, if – according to the nurse’s judgement - the person understood the implications of lifelong ART, he/she will be offered to start ART immediately. Those who decide to start ART during the visit or intend to start within 7 days will receive a 30-day ART-supply and a follow-up appointment at the clinic within 12 to 16 days. Choice of ART regimen and use of cotrimoxazole prophylaxis follows national and international guidelines [36, 37]. Participants with a CD4 cell-count < 100 cells/mL will receive testing for cryptococcal antigen. In case of a positive result, the participant will be treated according to guidelines and excluded from the study. In order to reduce travel time and transport cost, participants who are clinically stable, will have their follow-up visits and ART refills more widely spaced with appointments at 6 weeks, 3, 6, (9) and 12 months after ART initiation. Participants are, however, encouraged to visit the clinic at any time in case of problems or questions.

Figure 1 summarizes flow of participants in the study.

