**Table Taba:** 

Service provided	Control group	Intervention group
Baseline laboratory values (creatinine, CD4-count, haemoglobin)	Blood taken at first clinic visit after the positive HIV test result, results communicated at second clinic visit.	Performed in the community the day of the HIV test result as point-of-care
Adherence-counselling	At first and second clinic visit	In the community, directly after the HIV test result
ART-initiation	After at least two adherence counselling sessions at the clinic	Proposition of starting the same day as tested HIV positive
Follow-up visits and drug-refills at the clinic	Monthly	2 weeks – 6 weeks – 3–6–9–12 months

Table 1 Overview of services provided after a positive HIV test result during community-based HTC campaigns in the control and intervention group

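### A positive cryptococcal antigen result excludes participants after allocation, on a test whose timing differs by arm, in conflict with the stated intention-to-treat analysis

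*Protocol article*

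**What the plan says.** All references are to the Methods of the protocol article.

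- **Recruitment and participants.** The exclusion criteria end with "or a positive cryptococcal antigen test". No arm is named.
- **Control and intervention arms, intervention.** The paragraph opens: "Participants randomized to the intervention group receive post-test counselling and clinical and laboratory assessment with the possibility of same day ART start". The study nurse's point-of-care CD4 count is part of that assessment. Then: "Participants with a CD4 cell-count < 100 cells/mL will receive testing for cryptococcal antigen". And: "In case of a positive result, the participant will be treated according to guidelines and excluded from the study".
- **Control and intervention arms, control.** At the household, "individuals found HIV-positive and randomized to the control arm will receive post-test counselling and a referral letter with an appointment at their chosen health facility". The CD4 count comes later: "On the first visit to the clinic, the participant receives a laboratory assessment (CD4 cell-count, serum creatinine, haemoglobin) and a first adherence counselling session". The overview table of services agrees: "Blood taken at first clinic visit after the positive HIV test result, results communicated at second clinic visit". No CrAg test is described for controls.
- **Primary outcomes.** Linkage to care means at least one clinic attendance within 90 days of enrolment.
- **Sample size and randomization.** "Analysis will be as intention to treat". Non-linkers count as failures for viral suppression.

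**The concern.** An entry criterion that rests on a laboratory result should be determined in the same way in both arms, before allocation. Here the result that triggers the CrAg test exists on day 0 in one arm only. In the other arm it exists only for people who come to the clinic.

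If the exclusion is carried out as described, participants with advanced disease leave the intervention arm on day 0. Comparable controls either stay, because they are not tested, or leave only after attending. A control excluded on a test from a visit within 90 days is by definition a linkage success, so that exclusion is conditional on the first primary outcome.

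Both primary outcomes are proportions of the randomised participants, so who remains in the denominator matters. At stake is whether the analysed groups are the randomised groups, which the intention-to-treat statement promises.

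**Working it through.** **1. The plan's own figures.** Inputs from Sample size and randomization: 40% and 60% linkage, 5% type I error (taken as two-sided), 90% power.

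n per arm = [1.96·√(2·0.5·0.5) + 1.2816·√(0.4·0.6 + 0.6·0.4)]² / 0.2² = (1.3859 + 0.8879)² / 0.04 = 129.3, so 130 per arm and 260 in total. This matches the plan. Power for 25% against 45% with 130 per arm is 92.7%, matching the stated 93%. Nothing below changes either figure.

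**2. Order of events.**

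| | Intervention | Control |
|---|---|---|
| CD4 count | after allocation, day of HIV test, at home | first clinic visit |
| CrAg test | if CD4 is below the stated threshold | not described |
| Who can be excluded on CrAg | any CrAg-positive participant | at most those who attend |

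Reading the rule as covering both arms does not remove the difference, because a control cannot be identified before attending.

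**3. Size for linkage.** The documents give no CrAg frequency. Assume k = 1, 2 or 3 CrAg-positive people per arm, with 130 per arm and the planned rates (78 linked against 52 linked).

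- Intervention, excluded people would not have linked: 78/(130 − k) = 60.5%, 60.9%, 61.4%.
- Intervention, excluded people would have linked: (78 − k)/(130 − k) = 59.7%, 59.4%, 59.1%.
- Control, positives link at 40% and those who link are excluded: (52 − 0.4k)/(130 − 0.4k) = 39.8%, 39.6%, 39.4%.
- Control, all positives link and are excluded: (52 − k)/(130 − k) = 39.5%, 39.1%, 38.6%.
- Control, nobody excluded: 40%.

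Apparent difference in percentage points (true difference 20):

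| | Assumption | k = 1 | k = 2 | k = 3 |
|---|---|---|---|---|
| A | intervention positives link at 0%, control positives at 40%, linked controls excluded | 20.7 | 21.3 | 22.0 |
| B | intervention positives link at 0%, no control excluded | 20.5 | 20.9 | 21.4 |
| C | intervention positives link at 100%, control positives at 40%, linked controls excluded | 19.9 | 19.7 | 19.6 |
| D | intervention positives link at 100%, no control excluded | 19.7 | 19.4 | 19.1 |
| E | positives link at their arm's average (60%/40%), linked controls excluded | 20.2 | 20.4 | 20.6 |
| F | positives link at 100% in both arms, linked controls excluded | 20.2 | 20.3 | 20.5 |

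Rows A and C give these people different linkage behaviour in the two arms, so they are outer bounds. B also covers 0% linkage in both arms, since then no control is ever tested. The like-for-like rows B, E and F run from 20.2 to 21.4.

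**4. A second bound.** Assume 5–20% of participants have a CD4 count below the threshold and 2–15% of those are CrAg-positive. The excluded fraction is then e = 0.1% to 3.0%, or 0.1 to 3.9 of 130. At e = 3%:

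- Intervention linkage reads between (0.60 − 0.03)/0.97 = 58.8% and 0.60/0.97 = 61.9%.
- Intervention viral suppression reads between (0.45 − 0.03)/0.97 = 43.3% and 0.45/0.97 = 46.4%.
- With no true effect (40% in both arms), intervention-only exclusion and every excluded person a would-be failure, intervention linkage reads 0.40/0.97 = 41.2%. The two-sided type I error is about 5.5% instead of 5.0% (5.05% at e = 1%).

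**The case against.** The strongest reply is that leaving the study is not the same as leaving the analysis. The intention-to-treat statement carries no exception. Where the article does drop people from an analysis, as with transfers out in the secondary outcome on retention, it says so. A condensed article may leave the definition of analysis sets to a fuller document, and the flow chart that might show the order is not available here. This stands in part: a reader might infer that the analysed arms are certain to differ from the randomised arms, and the text does not establish that. But the benign reading is not stated either, and it sits badly with CrAg being listed as an eligibility exclusion. The article prints both rules and does not reconcile them.

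A reader might also infer that the exclusion must favour the intervention. The documents do not support this. Linkage needs only one clinic attendance, and CrAg-positive participants are to be treated, which may itself bring them to a clinic. If they would have linked, removing them lowers intervention linkage (rows C and D). Only the control-side effect on linkage has a fixed sign: excluding controls at a visit within 90 days lowers control linkage. That applies only if controls are excluded at all, which the article does not describe.

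The objection that the effect is small also stands: at most a few participants per arm under the assumed ranges.

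**Conclusion.** The point holds as a conflict in the plan. As written, CrAg exclusion occurs after allocation, depends on arm and, for controls, can occur only after clinic attendance. This contradicts the stated intention-to-treat analysis.

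Its size rests wholly on assumption, because CrAg frequency is not in the documents. With 1 to 3 positives per arm, the apparent 20-point linkage difference lies between 19.6 and 22.0 points when linked controls are excluded as well (rows A and C), and between 19.1 and 21.4 when only intervention participants are (rows B and D). The 22.0 end should not be read as an expected bias: it needs these people never to link under the intervention yet to link at 40% under control. The sample size of 260 households and the 93% power are unaffected. The reason to act is that the denominators of both primary outcomes are left open to an arm-dependent rule, and that settling it costs almost nothing.

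**What to change.** 1. State that every randomised participant stays in the analysis set of the allocated arm for both primary outcomes, whatever a CrAg result obtained after allocation shows.
2. Optionally, add a sensitivity analysis without participants known to be CrAg-positive, noting that they are identified differently in the two arms.
3. Reconcile the exclusion criteria, the descriptions of both arms and the intention-to-treat statement on when CrAg eligibility is determined, and say what exclusion from the study means for follow-up and for analysis.

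A reader might go further and ask for CrAg to be deleted from the exclusion criteria. The analysis problem does not require that. The eligibility rule and the clinical care of these participants remain for the investigators to decide.

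The cost is a few sentences and outcome ascertainment for a handful of people. The downside is that a few participants whose ART may be deferred stay in the denominators.
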